Once the baseline evaluations have been completed, participants will be randomized into different groups to reduce the risk of bias during the assessment. A computer-generated randomization sequence stratified by two factors (age at study entry and sex) will allocate participants to each group. This randomization sequence will be created by a blinded researcher external to the project using computer software. The allocation will be concealed in a password-protected computer file.

The groups will undergo pre-test (before the intervention), post-test (after each intervention), and follow-up (after an 8-week detraining period) measurements.

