The IG1 (supervised exercise program) will undergo an exercise program twice per week (45 min per session) for 8 weeks. Each session will include a warm-up (5 min), muscle-strengthening exercises (35 min), and a cool-down (5 min, stretching exercises). The program will focus on core muscles, starting with low-intensity isometric contraction for trunk stabilization and mobility exercises, then increasing intensity with functional tasks. Exercise intensity will be moderate-to-vigorous, assessed via the RPE scale [42], ensuring no pain is felt. This scale will be visible to participants during sessions. Each exercise will last 60 s, followed by 60 s rest. Execution speed will be individualized to each participant’s physical condition and tolerance. Exercises will follow a fixed order with progressive difficulty, as described in previous literature [32,43]. This progression will be structured according to the following phases [32]. (i) *Phase 1* (3 sessions, ≥5 RPE): mobility, isometric, and motor control exercises that will include full body, with special emphasis on the core, particularly isometric contraction of the transversus abdominis muscle. Participants will be instructed to place their hands on the lower abdomen during the exercises to perceive the contraction through kinesthetic feedback and facilitate correct transversus abdominis activation (ii) *Phase 2* (4 sessions, ≥5 RPE): co-contraction and functional tasks involving deep trunk muscles. (iii) *Phase 3* (4 sessions, ≥6 RPE): functional task with greater difficulty or intensity, including load. (iv) *Phase 4* (5 sessions, ≥6 RPE): functional task performed on an unstable surface.

A detailed description of the exercise intervention is shown in Table 3 and Table 4. Participants will receive real-time feedback on posture correction and examples for exercise familiarization. Strategies to improve exercise adherence will include: (i) a positive and dynamic session environment; (ii) an attendance control system to minimize dropouts.

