The CG will receive the usual care provided by the Physical Medicine and Rehabilitation Service. Participants will follow the same session structure described above twice per week (45 min per session) for 8 weeks. All participants will perform 1 set of 10 repetitions or 60 s per exercise, followed by 60 s of rest. Execution speed will be individualized. Intensity will be assessed with an RPE scale (≥5 RPE). Sessions will include: warm-up (5 min: postural awareness, diaphragmatic breathing, costal breathing, transversus abdominis contraction, pelvic swing); main activity (35 min: lower/upper abdominis exercise, hip abduction with knee extension, cat-camel exercise, alternate arm/leg elevation in quadruped, bird-dog); and cool-down (5 min: lumbosacral, psoas, hamstring, and pyramidal muscle stretching, bird-dog, and lumbosacral stretching on the floor). All of them will be performed in supine or quadrupedal position. Although active, this protocol reflects hospital standard rehabilitation care. Including it in the control group meets ethical and organizational requirements, ensuring participants are not deprived of care, allowing a more rigorous comparison with the multidimensional intervention.

This program allows adaptations for practical evidence-based aspects, such as performing an alternative exercise targeting the same muscle group without causing pain or changing the plane of movement. Adverse events, effects, or health issues attributable to the testing or intervention sessions, along with their severity and resolution, will be recorded by a researcher responsible for auditing the assessment team. If an adverse event prevents participation, temporary or permanent exclusion will be discussed and documented. Temporary exclusions require medical clearance for return.

This study was approved by the Clinical Research Ethics Committee of Granada, Government of Andalusia, Spain (code: 2255-N-21). It will be conducted following the ethical principles of the Declaration of Helsinki (1964 and later amendments). No formal audit is scheduled for this clinical trial.

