## 4. Statistical Analysis

Since this study aims to determine the potential efficacy and effectiveness of supervised exercise programs and mindfulness, statistical analysis will be performed using both per-protocol and intention-to-treat approaches (with ≥70% attendance required for inclusion). The effects of the intervention will be assessed as between-groups differences in changes from baseline to post-intervention in primary and secondary outcomes using one-way analysis of covariance (ANCOVA). The mean change (post-intervention minus baseline values) will be used as the dependent variable, the group as the fixed factor, and the baseline value of the outcome as a covariate. The same approach will be applied to evaluate the persistence of changes at follow-up. Given the repeated-measures design, linear mixed models will also be used to examine group-by-time interactions across all time points. This approach accommodates missing data under the missing-at-random assumption and accounts for within-subject correlation, providing a more robust framework than ANCOVA for longitudinal analyses. All analyses will be adjusted for potential confounding variables that are not well balanced at baseline. Sex will be used as a potential covariate in all analyses to explore whether the intervention effects differ between men and women, and whenever possible, the sample will be stratified by sex. Cohen’s d will be calculated to determine standardized effect sizes. To control for type I error due to multiple comparisons, the Bonferroni correction will be applied when conducting post hoc analyses or when evaluating multiple outcome variables. Statistical significance will be set at α = 0.05. All analyses will be performed using the Statistical Package for the Social Sciences (SPSS) for Windows, Version 27.0. (IBM Corp., Armonk, NY, USA).

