### 5.1. Strengths

This protocol advocates for a multidimensional approach (supervised exercise and mindfulness) as a key strategy to optimize pain, disability, muscular fitness, quality of life, mental health, and gait parameters in individuals with CPLBP, aiming to achieve clinically relevant improvements. A notable strength of this study design is its use of a multidimensional approach with an active control group for treating CPLBP. Additionally, various measures will be used to assess both the physical and mental health status of the individuals, allowing for a comprehensive evaluation of the intervention’s potential effects. Fitness will be assessed through field tests, which, if proven beneficial, could have significant implications in clinical practice. Furthermore, the study will use objective measures (triaxial accelerometers) to examine associations between PA and sedentary behavior in this population. In addition, several potential challenges have been anticipated. Participant dropouts, particularly during the short-term follow-up period, will be addressed through regular contact, reminder communications, and flexible scheduling of assessments. To promote adherence to the intervention protocols, all sessions will be supervised, and attendance will be monitored. Variability among therapists will be minimized through standardized training and the use of detailed intervention protocols. Finally, while the study population may limit generalizability, the inclusion criteria were carefully selected to reflect real-world clinical populations with CPLBP.

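### The adverse-event rule in section 2.4 does not separate stopping sessions from leaving the trial, so it permits loss of post-test and follow-up outcomes for people who worsened

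*Protocol article*

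**What the plan says.** Section 2.4 (Intervention) provides that "Adverse events, effects, or health issues attributable to the testing or intervention sessions, along with their severity and resolution, will be recorded". It then states: "If an adverse event prevents participation, temporary or permanent exclusion will be discussed and documented". The next sentence adds: "Temporary exclusions require medical clearance for return". Neither sentence says whether exclusion is from sessions, from assessments or from the trial.

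Three other places bear on the point:
- Section 2.3 sets the assessments: "The groups will undergo pre-test (before the intervention), post-test (after each intervention), and follow-up (after an 8-week detraining period) measurements". Table 1 marks t1 and t2 for the pain and disability measures. Neither mentions people stopped by an adverse event.
- Section 5.1 says that dropouts "will be addressed through regular contact, reminder communications, and flexible scheduling of assessments".
- Section 4 announces "both per-protocol and intention-to-treat approaches (with ≥70% attendance required for inclusion". It says of the linear mixed models: "This approach accommodates missing data under the missing-at-random assumption".

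**The concern.** The rule uses one word for two different acts. Ending the sessions is a treatment matter. Ending outcome assessment is a data matter and need not follow from it. If exclusion is applied as removal from the trial, the t1 and t2 values of that person are never collected, and no choice of analysis set made later can recover them.

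Pain and disability are primary outcomes, and a pain flare is a foreseeable reason why someone cannot continue exercising. The loss would then depend on the outcome itself. The ANCOVA uses the change from baseline to post-intervention, so a person without t1 contributes nothing to it. The mixed model relies on missing at random. That is hard to defend where the cause of the missing value is worsening after baseline that the modelled visits (t0, t1, t2) do not contain. Pain scores are also taken around each session (section 3.1.1), but section 4 does not say that they enter the model.

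The trial would also lack its scheduled 2-month assessment for the people whose course after an adverse event is of most interest.

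**Working it through.** **1. What does exclusion cover?** Two readings, side by side.

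- *Pause or end of sessions.* The sentence stands in the intervention section, shortly after text on adapting exercises. A temporary exclusion with a return fits a pause.
- *Leaving the trial.* The preceding sentence covers harm from testing as well as from sessions, so the participation that is prevented can include the assessments. The Abstract uses nearly the same phrase, preventing participation, for people kept out of the study. A permanent exclusion has no return, and nothing assigns such a person a later assessment.

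Both readings are natural. Section 2.3 and Table 1 schedule visits for the groups without saying that excluded people stay in them. Section 5.1 deals with participants who drop out, not with those whom the team excludes. None of these settles the matter.

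**2. Size if outcomes are lost.** The plan has no figure for losses through adverse events. Inputs from section 2.2 are 35 per arm, an effect size of 0.70 (read here as a standardised mean difference) and a dropout of 20–30%. The 35 follows from the stated 26 at 25% dropout: 26 / (1 − 0.25) = 34.7, rounded up to 35. The plan thus allows for 35 × 0.20 = 7 to 35 × 0.30 = 10.5 losses per arm. That allowance protects power and does nothing against bias.

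Assumed: k people in an arm are lost after an adverse event, and their mean change is g SD worse than the mean m of those who remain.

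True arm mean = [(35 − k) × m + k × (m − g)] / 35 = m − k × g / 35

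Overstatement when only the remaining people are used = k × g / 35

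| k lost | g = 0.5 | g = 1.0 | g = 1.5 |
|---|---|---|---|
| 1 | 0.014 | 0.029 | 0.043 |
| 2 | 0.029 | 0.057 | 0.086 |
| 3 | 0.043 | 0.086 | 0.129 |
| 5 | 0.071 | 0.143 | 0.214 |

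The range is 0.01 to 0.21 SD, or 0.014 / 0.70 = 2% to 0.214 / 0.70 = 31% of the planned effect. Two people at 1 SD give 0.057 / 0.70 = 8%. This is the shift in one arm. It passes in full to a between-group difference only if the other arm has no such shift.

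**3. Would the data be used if collected?** IG1 and the control group train "twice per week (45 min per session) for 8 weeks", that is 2 × 8 = 16 sessions. The attendance condition asks for 0.70 × 16 = 11.2, so 12 sessions. Five missed sessions (2.5 weeks) remove the person. In IG2, if mindfulness sessions count, the total is 16 + 8 = 24 and 0.70 × 24 = 16.8, so 17 are needed and eight missed sessions remove the person. As section 4 is worded, the condition also applies to the set called intention-to-treat. Someone stopped permanently before the threshold would be left out of the analysis even with complete t1 and t2 data.

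**The case against.** The strongest reply is that the text never says assessments stop. Exclusion is only to be discussed, it may be temporary, and the talk of return suggests a pause in sessions. The visit schedule makes no exception for people who stop, and section 5.1 plans contact and flexible scheduling. The article condenses a fuller protocol, which may say that discontinued participants are followed. A flare would not go unseen either, because pain is rated before and after each session and attributable events are recorded with severity and resolution.

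Most of this stands, and it limits the point. A reader might infer that people harmed by the programme leave follow-up under this plan. The documents do not say that; they leave it open. A reader might also infer that the arm causing more harm will look better because IG1 and IG2 progress to load and unstable surfaces. IG2 follows the same exercise programme as IG1, so that argument has no force between those two arms. It could apply only against the control group. Even there the exertion values are minimums, the first two phases in IG1 and IG2 share the control group's minimum of 5, and no event rates are given.

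What does not stand is that this is mere silence from condensing. The article states a rule, and its wording can be read either way. Session pain scores and adverse-event records do not replace the t1 and t2 primary outcomes.

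**Conclusion.** The point holds as a defect of wording with a possible effect on the data. Section 2.4 permits, but does not prescribe, loss of t1 and t2 outcomes for people who worsened, and nothing in section 2.3, section 5.1 or Table 1 prevents it.

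The illustrative size is 0.01 to 0.21 SD in one arm. It rests on three assumptions: 1 to 5 of 35 people are lost, they do 0.5 to 1.5 SD worse than the rest, and the analysis uses only those who remain. If those lost do no worse than the rest, the bias is zero. A reader who assumed a 2 SD gap would get 1 × 2 / 35 = 0.06 to 5 × 2 / 35 = 0.29 SD, but the article supports no gap that wide. The direction of any bias in the between-group comparison cannot be settled from the document.

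The change is worth making because it is cheap and outcomes not collected cannot be recovered. It alters the analysis only if the attendance condition is also lifted from the intention-to-treat set.

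**What to change.** 1. In section 2.4, replace exclusion after an adverse event with temporary or permanent discontinuation of intervention sessions. Leave who stops and who is cleared to return exactly as written.
2. Add that these participants stay in the trial and are invited to t1 and t2 as scheduled. If the physical tests are not cleared, collect at least the questionnaires, including the Oswestry Disability Index, and the pain VAS taken on arrival.
3. In section 4, state that the intention-to-treat analysis includes these participants regardless of attendance, and keep the 70% condition for the per-protocol analysis only.

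The cost is a few sentences. Both visits are already scheduled for every group, and section 2.3 already has participants complete questionnaires at home. The small downside is the extra effort of contacting people who have stopped sessions. Measures that need physical testing may still be missing for some of them.

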## 3. Results

### 3.1. Primary Outcome Measures

#### 3.1.1. Pain-Related Measures

##### Pressure Pain Threshold

Algometry will be used to measure pain threshold using a hand-held standard pressure algometer (FPK 20, Wagner Instruments, Greenwich, CT, USA) [46]. Two measurements will be conducted twice, bilaterally, lying in the prone position. Each measure will be assessed in the middle side between L1–L5, 5 cm apart from the lumbar spinal processes [47,48,49]. Pressure pain threshold (PPT) will be defined as the minimum pressure perceived as painful by the participant, who will be instructed to say “stop” upon the onset of pain sensation [49]. To minimize the risk of temporal summation, PPT measurements will be taken twice at each site with a 30-s interval between assessments, and the average value will be used for data analysis. Static measures of PPT, or the point where stimulation just becomes painful, have demonstrated good to excellent reliability [50].

##### Perceived Acute Pain

A visual analogue scale (VAS) will be used to measure subjective changes in back pain intensity and unpleasantness. Testing will be performed at arrival and immediately after performing each physical fitness test during assessment [51]

A numerical rating scale (NRS) will be used to assess the pain before and after each intervention session. It is a 0–10-point scale, where 0 indicates “no pain” and 10, the “worst imaginable pain” [52].

##### Disability Due to Pain

The Oswestry Disability Index (ODI) will be used to measure pain disability. It is a valid and reliable self-administered questionnaire, specific for LBP, that measures limitations in activities of daily living [55]. It consists of 10 questions that are rated from 0 to 5 (from least to most limited). The total score (0–100%) is calculated by dividing the sum of the individual item scores by the maximum possible score and multiplying by 100. The interpretation of the results is as follows: 0–20% indicates minimal functional limitation; 20–40%, moderate limitation; 40–60%, severe limitation; 60–80%, disability; and above 80%, maximum functional limitation.

### 3.2. Secondary Outcome Measures

#### 3.2.1. Body Composition

Weight (kg), fat (%), skeletal muscle mass (kg), and fat mass (kg) will be measured by 8-point tactile-electrode bioimpedance (InBody R20, Biospace Gateshead, Kent, UK). The validity and reliability of this instrument have been previously reported [56]. Height will be assessed with a height rod (Seca 22). Moreover, waist [57] and neck circumferences [58] will be measured with a measuring tape (Seca 201).

#### 3.2.2. Muscular Fitness

The Biering–Sørensen test [59] will be used to evaluate back-extensor muscle strength. This test is commonly used to assess the endurance of the back and hip muscles, which are inversely associated with the presence and severity of LBP [60]. It is a trunk holding test in an antigravity prone position. The participant is placed in a prone position with the iliac crest at the edge of the stretcher. Two straps will be attached to the waist and the knees of the participant. At the investigator’s signal, the participant should try to keep the back in a horizontal position with hands at the side of the head as long as possible. Participants will perform only one trial, and the time will be recorded in seconds.

The Prone Bridging test [61] will be used to measure back-flexor muscle strength. It is a reliable isometric holding test in prone position with elbows under the glenohumeral joint, humeri joint perpendicular to the floor; head aligned with the cervical spine; trunk and pelvic floor in neutral position; knees extended and toes contacting the ground. Participants will keep this position as long as possible. When this position is maintained for 4 min, the test will be stopped. The test has demonstrated good reliability [62] and may serve as a useful indicator of core muscle endurance. Its performance time is inversely associated with the presence and intensity of LBP [63].

The 30-sec chair stand test will be used to evaluate the quadriceps, hamstrings, and gluteus muscle strength. It has shown good reliability in previous research with older adults and chronic-pain individuals [64]. Participants will be seated with their back straight on the chair, feet flat on the floor, and arms crossed and held against the chest. From this position, participants will rise to a full standing position and then return to the sitting position, as many times as possible in 30 s.

Hand dynamometry (5101 TKK handgrip dynamometer) will be used to measure upper body muscle strength. Participants will stand with shoulder abduction ~10 cm separated from the body, extended elbow, and the wrist in neutral position. The participant will press the dynamometer with maximum muscle contraction for 3–5 s without any additional body movement. The best score from both hands will be averaged. Previous research has shown a significant association between handgrip strength and CLBP [61] in these individuals. This test has shown good reliability in older adults [65]

#### 3.2.3. Motor Agility

The 8-foot up-and-go test will be used to measure motor agility. Participants had to stand up from a chair, walk 2.44 m to and around a cone, and return to the chair in the shortest period of time. The best time from the two trials will be recorded. The 8-foot up-and-go test is a reliable and validated tool commonly used to assess motor agility in a safe manner [64].

#### 3.2.4. Gait Parameters

The high-density photoelectric cell platform, Optogait™ (Optogait; Microgate, Bolzano, Italy), will be used to evaluate spatiotemporal gait parameters, such as contact time, cadence, gait velocity, stance, support time, and stride length. Optogait™ has been demonstrated to be a valid and reliable method to assess gait parameters [66,67]. Participants will be informed to walk comfortably and repeat the circuit until a total of 200 steps is registered.

#### 3.2.5. Device-Measured Physical Activity and Sedentary Behaviour

The triaxial ActiGraph GT3X+ accelerometer (Actigraph, Inc., Fort Walton Beach, FL, USA) will be used to objectively assess PA and sedentary time. Participants will wear the accelerometer for 9 days (24 h a day) except during water activities. Days of device receipt and return (non-complete days) will be excluded from the analyses [68]. A minimum of 10 h of wear time per day and a total of 7 days with valid data will be required [69]. The accelerometer will be worn on the dorsal surface between the ulnar and radial styloid of the non-dominant wrist, tied with an elastic strap. It is suggested that wrist placement can help reduce selection bias and present minimal discomfort during sleep [70]. Accelerometer wear-time will be calculated by subtracting sleep and nap time (through a diary where participants reported the time they went to bed and the time they woke up) from each day. Participants will also record daily shower and/or water activities time in a diary [69,71,72]. Total time in sedentary behavior, light and moderate-to-vigorous PA (min/day) will be calculated based upon the recommended vector magnitude cut point [69,72].

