### 2.3. Recruitment and Randomization

Participant recruitment will take place at the Physical Medicine and Rehabilitation Service of Virgen de las Nieves University Hospital in Granada (belonging to the Andalusian Health Service). Individuals referred to the Rehabilitation Unit by their medical specialist and placed on a waiting list will receive information about the possibility of participating in this RCT via email or a telephone call. The diagnosis of CPLBP will be conducted by medical specialists in Physical and Rehabilitation Medicine, with advanced training and extensive clinical experience in musculoskeletal disorders. Subsequently, those initially interested in participating will be invited to an informational session where the study will be explained, and any concerns that may arise will be addressed. The estimated recruitment period for selecting participants will be from 1 to 3 months. Additionally, all interested individuals will be provided with written information about the study.

Individuals who agree to enroll in the study will be asked to read and sign a written informed consent that allows them to withdraw at any time. A unique code will be assigned to each participant to ensure their anonymity. On the first evaluation day, participants will report to the Multidisciplinary Laboratory in the Faculty of Sport Sciences (Granada) and will complete the following assessments: clinical information survey, blood pressure, resting heart rate, body composition, pain threshold, physical fitness, and gait parameters. The initial survey (anamnesis) will be conducted through face-to-face interviews by trained staff in order to collect data on sociodemographic characteristics (age, marital status, educational level, and current occupation), medical records and comorbidities, medicine consumption, and health habits (tobacco, alcohol, etc.). The Spanish version of the PAR-Q (C-AAF) [40] will be used to detect individuals who should undergo a medical examination before doing any type of PA. Individuals will not be required to perform any additional physical exercise or receive treatment for CPLBP upon starting this RCT. Participants will receive an accelerometer and several health-related questionnaires to complete at home on the same day of the evaluation. Participants will be asked to return the accelerometer and questionnaires nine days later. As a reward, they will receive a report for each assessment they attend.

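### Accelerometer wear time is defined as waking time, so the 10 h rule screens almost nothing; if non-wear is detected instead, requiring 7 valid days leaves no spare day, or one at most

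*Protocol article*

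**What the plan says.** Section 3.2.5 of the protocol article sets the wear period: "Participants will wear the accelerometer for 9 days (24 h a day) except during water activities". It then removes the first and last days: "Days of device receipt and return (non-complete days) will be excluded from the analyses". The validity rule is "A minimum of 10 h of wear time per day and a total of 7 days with valid data will be required".

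Wear time has its own formula: "Accelerometer wear-time will be calculated by subtracting sleep and nap time" from each day, with bed and wake times taken from a participant diary. On water, the section says "Participants will also record daily shower and/or water activities time in a diary", but not that this time is subtracted. Sedentary, light and moderate-to-vigorous minutes "will be calculated based upon the recommended vector magnitude cut point"; the value is not given. The section describes no device-based detection of non-wear and does not exclude one.

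Section 2.3 gives the return date: "Participants will be asked to return the accelerometer and questionnaires nine days later". Section 4 specifies ANCOVA on change from baseline and adds linear mixed models, of which it says "This approach accommodates missing data under the missing-at-random assumption". Device-measured activity and sedentary time are secondary outcomes.

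**The concern.** A wear-time criterion is meant to separate days on which the device was on the wrist from days on which it was not. The stated formula has no term that can do this, because length of day and diary sleep are the same whether the device was worn or left on a table. The 10 h threshold is therefore applied to a quantity that hardly responds to wear.

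The consequence depends on what is done in practice, and there are two branches:

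- **The formula is applied as written.** Invalid days are not caught. A still device records no movement, so those minutes would fall below a movement cut point and be counted as sedentary.
- **Non-wear is detected by some other step.** The sentence on wear time is then wrong, and the 7-day requirement becomes demanding, because it uses all or nearly all of the complete days.

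At stake are the validity of the sedentary and activity outcomes in the first branch, and the number of participants contributing to them in the second. The Introduction itself cites a need for more rigour in accelerometry in this population.

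**Working it through.** **1. Complete days available**

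- Section 3.2.5: 9 days worn − 2 (receipt and return) = 7 complete days; 7 required; 0 spare.
- Section 2.3, counting receipt as day 0 and return as day 9: days 1 to 8 = 8 complete days; 7 required; 1 spare.

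**2. What the wear-time formula returns**

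Formula: wear = 24 h − diary sleep and naps. Removal needed to fail the day = wear − 10 h. Sleep length is an assumption; the article gives none.

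| Sleep (h) | Wear by formula (h) | Recorded and subtracted removal needed to fall below 10 h |
|---|---|---|
| 6 | 18 | 8 |
| 8 | 16 | 6 |
| 10 | 14 | 4 |

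A day with no recorded removal always passes. Even if diarised water time were subtracted, it would have to exceed 4 to 8 h before the day failed.

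**3. Effect on sedentary time if the formula is applied literally (inference)**

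Each hour of unrecorded waking removal would add 60 min to that day's sedentary total. Averaged over 7 days that is 60/7 ≈ 8.6 min/day. The error is only the part of that hour in which the participant was not in fact sedentary.

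**4. Retention if non-wear is detected**

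Assumptions: each day is valid with probability p, independently. The article gives neither. Formulas: 7 of 7 at one visit = p^7; at baseline and post-test = p^14; at all three visits = p^21; at least 7 of 8 = p^8 + 8p^7(1 − p).

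| p | 7 of 7, one visit | 7 of 7, baseline and post-test | 7 of 7, all three visits | 7 of 8, one visit |
|---|---|---|---|---|
| 0.95 | 69.8% | 48.8% | 34.1% | 94.3% |
| 0.97 | 80.8% | 65.3% | 52.7% | 97.8% |
| 0.98 | 86.8% | 75.4% | 65.4% | 99.0% |
| 0.99 | 93.2% | 86.9% | 81.0% | 99.7% |

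Out of 35 randomised per arm, 7 of 7 at one visit is 24.4 participants at p = 0.95 and 32.6 at p = 0.99, before any dropout. The change-score ANCOVA needs baseline and post-test, so the paired column applies to it. With 8 complete days the paired figure at p = 0.95 is 0.943² = 88.9%. At least 4 valid days of 7 keeps 99.7% at one visit even at p = 0.90.

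**5. Price of fewer days**

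Reliability of a k-day mean = k·r / (1 + (k − 1)·r), with single-day ICC r = 0.5 (assumption):

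- k = 7: 3.5/4 = 0.875
- k = 4: 2/2.5 = 0.80

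**The case against.** The strongest reply is that a journal article condenses. A non-wear algorithm may sit in the full protocol, the analysis plan or the cited processing methods, and its absence here is no finding. That is fair for the algorithm. It does not rescue the sentence on wear time, which states a formula. If another method is used, the sentence is incorrect.

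Four further points stand and limit the concern.

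- A reader might infer that the plan scores device removal as sedentary. It does not say so; that follows only from literal application of the formula and cut point.
- A reader might infer that a missed day both removes the participant and inflates sedentary time. For the same missed time these are alternatives. Under the literal formula an unrecorded missed day still gets 14 to 18 h of wear and stays valid. If it is detected, it does not contaminate sedentary minutes.
- A reader might take the 49% paired figure as the expected retention. It holds only at p = 0.95 with independent days. Round-the-clock wrist wear and a 10 h threshold make higher validity plausible, and if poor wear clusters within people, more would pass at the same average validity. Nothing in the article shows a large loss or one that differs between arms.
- The loss is confined to secondary outcomes at that visit. The mixed model can use the participant's other visits, although missing at random is open to doubt if poor wearers differ in activity.

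Requiring a full week is also a defensible design choice in itself. The difficulty is requiring it with little or no slack.

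**Conclusion.** The concern holds as a choice between two unsatisfactory readings. Section 3.2.5 defines wear time as waking time, so its 10 h rule screens almost nothing: 14 to 18 h is returned for an assumed 6 to 10 h of sleep, whatever the actual wear. On that reading, sedentary minutes can include unrecorded removal, by an amount the article does not allow one to estimate. If non-wear is detected instead, the 7-day rule leaves no spare day on Section 3.2.5's count and one on the other reading of Section 2.3. Under assumed independent per-day validity of 0.95 to 0.99, 70% to 93% pass 7 of 7 at one visit and 49% to 87% at both baseline and post-test.

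The article does not support reading this as loss of participants from the trial, or as a threat to the primary pain and disability outcomes. It is a correctable weakness in the processing rules for secondary outcomes.

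**What to change.** 1. Compute wear time from the device record with a stated non-wear detection rule. Use the diary for sleep and water time, and exclude non-wear from sedentary minutes.
2. Reconcile Sections 2.3 and 3.2.5 on whether 7 or 8 complete days are collected.
3. Set the valid-day minimum below the number available, for example at least 4 days of at least 10 h including a weekend day, and keep the 7-day rule as a sensitivity analysis. The 4-day figure is an illustration and has no source in the article.

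This needs a change of wording and some processing work, with no new data and no added burden on participants. The downside is slightly noisier activity means for those with fewer days: reliability of 0.80 instead of 0.875 at the assumed ICC of 0.5.
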